## Abstract

**Background:**

Current guidance regarding the role of daily breakfast in human health is largely grounded in cross-sectional observations. However, the causal nature of these relationships has not been fully explored and what limited information is emerging from controlled laboratory-based experiments appears inconsistent with much existing data. Further progress in our understanding therefore requires a direct examination of how daily breakfast impacts human health under free-living conditions.

**Methods/Design:**

The Bath Breakfast Project (BBP) is a randomised controlled trial comparing the effects of daily breakfast consumption relative to extended fasting on energy balance and human health. Approximately 70 men and women will undergo extensive laboratory-based assessments of their acute metabolic responses under fasted and post-prandial conditions, to include: resting metabolic rate, substrate oxidation, dietary-induced thermogenesis and systemic concentrations of key metabolites/hormones. Physiological and psychological indices of appetite will also be monitored both over the first few hours of the day (i.e. whether fed or fasted) and also following a standardised test lunch used to assess voluntary energy intake under controlled conditions. Baseline measurements of participants' anthropometric characteristics (e.g. DEXA) will be recorded prior to intervention, along with an oral glucose tolerance test and acquisition of adipose tissue samples to determine expression of key genes and estimates of tissue-specific insulin action. Participants will then be randomly assigned either to a group prescribed an energy intake of ≥3000 kJ before 1100 each day or a group to extend their overnight fast by abstaining from ingestion of energy-providing nutrients until 1200 each day, with all laboratory-based measurements followed-up 6 weeks later. Free-living assessments of energy intake (via direct weighed food diaries) and energy expenditure (via combined heart-rate/accelerometry) will be made during the first and last week of intervention, with continuous glucose monitors worn both to document chronic glycaemic responses to the intervention and to verify compliance.

**Trial registration:**

Current Controlled Trials ISRCTN31521726.

## Background

It is over four decades since Pavel Fábry and colleagues published their studies showing positive correlations between infrequent daily meal patterns and overweight, hypercholesterolaemia, impaired glucose tolerance and ischaemic heart disease [1]. Since then, it is certainly notable that the increased prevalence of overweight and obesity in Western Societies has been paralleled by a progressive decline in breakfast consumption [2]. However, subsequent scientific literature has not substantially progressed understanding beyond the initial cross-sectional associations published in the late 1960s. While subsequent cross-sectional and/or longitudinal investigations have undoubtedly clarified certain aspects of these correlations and confirmed such relationships across a wider population range, it is impossible to establish any degree of causality from these data due to major confounding variables; for example, the fact that frequent breakfast consumers also tend to exhibit numerous other healthful lifestyle choices such as lower fat/alcohol intakes, higher fibre/micronutrient intakes, not smoking and also a tendency to exercise more [3-11].

In terms of existing cross-sectional evidence linking increased adiposity with infrequent or insufficient breakfast consumption, the wealth of available literature does conform to the stated positive relationship [1,7,11-21]]. However, the majority of these large-scale epidemiological studies have involved self-reported dietary records, which are known to underestimate absolute energy intake to a greater extent for more overweight individuals [22]. Indeed, Summerbell *et al*. (1995) reanalysed the data from 3 existing studies across a range of age groups and found that the commonly reported associations between frequent daily meal patterns/high energy intake at breakfast and overweight do not persist once corrected for 'unreasonably low' energy intakes [23]. These corrected results therefore fall into agreement with the one other existing cross-sectional study which found no relationship between daily meal frequency and percent body fatness as determined by hydrostatic weighing, in which dietary records were managed on an individual basis via telephone [24]. Notwithstanding such methodological issues, it might be suggested that one benefit of a frequent meal pattern would be a lasting satiating effect, possibly related to the high fibre content of many breakfast foods [25]. Indeed, at least three intervention studies are consistent with this reasoning [26-28], although many cross-sectional studies have not observed any difference in overall energy intake between frequent and infrequent breakfast consumers [12,13,17,29] or have even found higher energy intakes associated with breakfast consumption [13,15,16,20]. These latter studies necessarily implicate some interaction between energy intake and energy expenditure (i.e. if breakfast consumers are leaner), although the only evidence for such an effect comes from the study by Wyatt *et al*. (2002), in which self-reported physical activity was higher amongst individuals who reported having breakfast on more than 3 days each week [29]. Ultimately, the balance of currently available cross-sectional evidence cannot provide information regarding the direction or even the existence of any causal relationship between breakfast consumption and weight change. Moreover, issues regarding the accurate measurement of changes in energy intake may even question the validity of these findings.

To gain greater insight into this field, it is necessary to move towards higher levels of evidence beyond simple cross-sectional observations. Fortunately, five of the studies that have documented baseline correlations between weight status and breakfast frequency have also conducted longitudinal examinations of breakfast habits and weight change over between 3 and 13 years in both children [11,18,20] and adults [19,21]. In contrast to the cross-sectional evidence detailed above, a far less consistent pattern of findings is apparent. Barton *et al*. (2005), Timlin *et al*. (2008) and Bazzano *et al*. (2005) have all reported a reduced prospective risk of weight gain with frequent breakfast consumption over 5-10 years follow-up in children [18], adolescents [11] and adults [19], respectively; while Kant and colleagues found no relationship whatsoever between weight change over 8-10 years and daily meal pattern either at baseline or at follow-up, although an infrequent daily meal pattern does not necessarily indicate that breakfast was omitted [21]. Interestingly, in that study the authors also note that daily meal pattern was unrelated to self-reported physical activity either at baseline or at follow-up, although no actual data are reported. The balance of longitudinal evidence in this area becomes yet more equivocal when considering the study by Berkey *et al*. (2003), in which a large cohort of children between the ages of 9 and 14 were monitored annually over three years [20]. Importantly, this study also stratified participants according to weight and actually found omission of breakfast to be positively associated with prospective weight *loss *in overweight children. In contrast, normal weight children in this study displayed a trend in the opposite direction in that more weight was *gained *over time when breakfast was always omitted rather than consumed. It is also noteworthy that recent longitudinal evidence has reported detrimental cardiovascular and metabolic health outcomes in association with breakfast skipping even when adjusted for physical activity status and increased body fatness [i.e. waist circumference; [30]]. Overall, the longitudinal studies summarised here question the causal nature of cross-sectional associations between breakfast and adiposity but also introduce the interesting possibility that the strength and direction of this relationship may be mediated by current weight status.

Evidence from randomised controlled trials in this area comes from a wide range of innovative research designs with varied research questions. Specifically, many of these studies have focused on either consuming a low energy breakfast or reducing the number of meals consumed on a daily basis, as opposed to the complete omission of breakfast *per se *[27,31,31-44]. In terms of the former, low energy breakfasts have been found to increase subsequent energy intake during a test meal 4 hours later [34] but not sufficiently to compensate for the reduced energy intake at breakfast [36,45]. In fact, even if overall energy intake is unaffected, it seems that reducing energy intake at breakfast for 6 weeks may actually result in greater reductions in body fat mass but lower overall weight loss due to the preservation of lean tissue mass [35]. Conversely, those studies which have varied the number of meals consumed on a daily basis from between 1 and 9 meals per day have found no effect on energy intake, resting energy expenditure or change in body mass [27,31-33,46-48], although one recent study has reported an increase in fat mass with omission of an afternoon meal for 28 days [47] and another has detected higher overall energy intake from meals of prescribed content during a 14 day period of breakfast omission [26]. The effects of varied meal frequency on dietary-induced thermogenesis (DIT) are even less consistent, with reports of DIT being either unaffected [27,40,41], increased [37,38] or in fact decreased [32,39] by an infrequent daily feeding pattern. In terms of selected health outcomes typically associated with chronic weight change, causal evidence is also inconsistent with what might be expected based upon cross-sectional observations. For example, there is some tentative evidence that a regular daily meal frequency (6-9 meals per day) for 2 weeks can improve insulin sensitivity and blood lipid profiles relative to more chaotic and/or less frequent feeding patterns [43,44]. It is therefore intriguing that intermittent 24 hour fasting every other day for 2 weeks also has the capacity to improve insulin sensitivity, even without any significant short-term reduction in body mass [49]. However, such alternate-day fasting also reduces resting metabolic rate, so may favour weight gain and associated consequences in the long-term [50].

Nonetheless, as mentioned previously, neither varied meal frequency nor reduced energy intake at breakfast necessarily precludes the ingestion of food in the morning to interrupt an overnight fast. It is therefore very interesting that so few randomised controlled trials have directly contrasted the impact of omitting breakfast (i.e. extending the daily overnight fast) from an otherwise matched diet in terms of components of energy balance and subsequent weight loss [26,46,51]. One of these studies has already been discussed in relation to the observed increase in energy intake when breakfast was omitted from the habitual diet [26] but also reported evidence of impaired glycaemic control and elevated blood lipids with breakfast omission, despite the fact that body mass was unaffected. These findings are consistent with the more recent work of Stote *et al*. (2007) in relation to changes in body mass over 8 weeks of extended morning fasting [46], along with metabolic data taken from the same study [52]. The third trial specific to inclusion/omission of breakfast from the habitual diet also involved prescribed dietary intake but with restricted energy intake (i.e. ~ 5000 kJ·d^-1^) over a period of 12 weeks, provided either as 3 meals each day (including a cereal breakfast) or with 2 meals each day (including an additional bran muffin with each meal to maintain energy/fibre intake) [51].

Importantly, the authors of this latter study also stratified participants according to their usual breakfast eating habits at baseline and found habitual breakfast consumers lost more weight by omitting breakfast while habitual breakfast non-consumers lost more weight by introducing breakfast. This study therefore indicates that the success of a weight loss programme can be mediated to an extent by the degree to which that programme differs from each individual's usual dietary habits but also revealed that not consuming breakfast increases the probability of impulsive snacking throughout the day, which is known to be associated with a poorer overall dietary profile [53]. It should be noted, however, that all three of the studies cited above have involved some degree of prescription or restriction in terms of dietary intake, so may not therefore be sensitive to potential 'real-world' alterations in eating behaviour and, furthermore, only the study by Stote *et al*. (2007) has attempted to quantify any effect of interventions on free-living energy expenditure. In that study, accelerometers (Actigraph™) were used to monitor weekly physical activity counts and it was reported that there was no evidence of any difference in physical activity between treatments [46]. However, this measurement tool has been shown to lack reliability when applied to free-living conditions [54] and may not therefore have been sufficiently sensitive to detect subtle alterations in spontaneous low-to-moderate intensity physical activity [55], which intuitively could be considered as the most responsive element of physical activity to modified eating patterns.

What becomes most clear when reviewing the above literature is that very few existing studies have actually attempted to quantify the impact of breakfast on the most malleable component of energy expenditure, namely physical activity energy expenditure [27,29,31,38,42,46]. Even amongst these six studies, it is notable that one simply reported cross-sectional associations based upon a self-administered physical activity questionnaire [29], while four others were randomised controlled trials that directly assessed energy expenditure using a whole-body calorimeter [although this method understandably restricts participants' spontaneous free-living physical activity; [27,31,38,42]]. Therefore, aside from the aforementioned study by Stote *et al*. in which overall physical activity level was estimated using accelerometers [46], only Verboeket-van de Venne *et al*. (1993) have provided data regarding changes in daily physical activities with varied feeding frequency (i.e. 2 versus 7 meals·d^-1^). Physical activity levels in that study were determined as the difference between resting energy expenditure measured using the whole-body calorimeter and average daily free-living energy expenditure measured using the doubly-labelled water technique, which revealed no effect of feeding frequency [38].

A central aim of this project is therefore to conduct a trial in accordance with current CONSORT guidelines which will employ contemporary measurement tools (i.e. combined heart rate and accelerometry) to generate objective and reliable data regarding physical activity energy expenditure under free-living conditions in response to varied daily meal frequency (i.e. daily breakfast versus extended fasting). In contrast to doubly-labelled water, this approach is not limited only to monitoring total energy expenditure but also permits specific evaluation of physical activity profiles in terms of the precise intensity and duration of various daily activities. This novel aspect of the work is complemented by both laboratory- and field-based assessments of all other components of energy balance, along with integration of various other techniques not previously combined in relation to this dietary intervention. In particular, changes in body composition will be accurately monitored via repeated DEXA scanning, continuous glucose monitors will provide a highly sensitive and meaningful analysis of glycaemic control with modified feeding patterns and, lastly, detailed blood/adipose tissue analyses will provide the most mechanistic information to date on this topic, thus establishing the existence and direction of any causal relationships between variables. In summary, there is some support for a positive relationship between extended daily fasting and energy balance, which can lead to a range of inter-related negative health consequences, and this project aims to address the casual nature of these associations via the following objectives:

*i.) To examine the impact of a single extended fast on the acute metabolic and behavioural mechanisms of short-term energy balance regulation.*

*ii.) To determine whether habitual extended fasting is causally related to chronic positive energy balance and establish the mechanisms through which this relationship may operate.*

*iii.) To translate the effects of habitual extended fasting into selected health outcomes related to chronic positive energy balance (i.e. adiposity, insulin resistance and cardiovascular disease).*

## Methods/Design

### Approach to the Research Question

As illustrated in Figure 1, extended daily fasting has the potential to impact upon adiposity, insulin resistance and cardiovascular disease via the acute influences of a single extended daily fast on a given day in terms of contributing to a more positive daily energy balance (***Objective i***) but also via the chronic metabolic and/or behavioural adaptations which may occur with habitual exposure to extended daily fasting over a more prolonged period (***Objective ii***). This project will take advantage of recent technological advances to comprehensively assess all aspects of energy balance and the physiological mechanisms which may underpin causal relationships between feeding frequency and energy balance (i.e. energy balance hormones). Furthermore, this approach of applying state-of-the-art analytical techniques to further progress current understanding will also provide valuable insight by examining selected health-related outcomes at a variety of levels ranging from molecular to whole-body (***Objective iii**)*. Specifically, many components and consequences of positive energy balance (e.g. poor dietary composition, sedentary behaviour and adiposity) have been well established as independent risk factors for insulin resistance and associated cardiovascular disease [56-58], with chronic low-grade inflammation strongly implicated in the latter [59]. In particular, systemic concentrations of C-reactive protein (CRP) have been shown to exhibit positive correlations with fasted glucose concentrations [60], atherosclerotic progression [61] and the incidence of initial coronary heart disease events [62]. It is therefore anticipated that the range of measures described below will address the stated objectives both from a basic and an applied science perspective to establish causal mechanisms and relationships to clinical outcomes, thus providing detailed yet practically valuable understanding in relation to public health policy and clinical practice.

**Figure 1 F1:**
[figure not shown]
**Proposed mechanistic pathway underlying the relationships between extended daily fasting, energy balance and health outcomes**.

### Trial Design

***Objective i ***will be addressed by way of an acute randomised cross-over comparison while ***Objective ii ***and ***Objective iii ***will be addressed via a chronic independent comparison of two parallel and randomly assigned groups, both involving a contrast between daily breakfast consumption and extended fasting. Figure 2 illustrates the course of progress through this trial consistent with current CONSORT guidelines for reporting randomised trials [63].

**Figure 2 F2:**
[figure not shown]
**Flow diagram illustrating progress through each phase of the trial [adapted from current CONSORT guidelines; **[63]**]**.

Lastly, any volunteer fulfilling all eligibility criteria (thus equivalent to the main study population) but unable to commit to the main study for other reasons (e.g. impossible to schedule trials in the required time-frame, unwilling to provide tissue samples, *etc*.) will be invited to participate as part of a 'true' control group. This group will complete only the free-living element of the study (Phase II; see later) while simply maintaining their usual lifestyle, therefore providing some background context regarding the extent to which the free-living measures themselves (i.e. dietary & physical activity monitoring) may impact outcomes but without necessitating any extended visits to the laboratory for tissue samples. These volunteers for the proposed work will be recruited from the local community (South West UK) via public advertisement (e.g. local press/radio) and will not be provided any financial incentive for participation. The protocol described herein was reviewed and approved by the National Health Service South West 3 Research Ethics Committee (10/H0106/13).

#### Inclusion Criteria

• Aged 21-60

• Body Mass Index 20-25 kg·m^-2 ^or >30 kg·m^-2^

• Able and willing to safely comply with all study procedures

• Able to provide written informed consent for participation

• Females must maintain a record of regular menstrual cycle phase or contraceptive use

• No anticipated changes in diet and/or physical activity habits during the study period (e.g. pre-planned holidays, diets/exercise plan, *etc*.)

#### Exclusion Criteria

• Any reported condition or behaviour deemed either to pose undue personal risk to the participant or introduce bias into the experiment

• Any reported use of substances which may pose undue personal risk to the participants or introduce bias into the experiment

• Any individual whose habitual lifestyle does not conform to a standard sleep-wake cycle (e.g. shift workers)

• Simultaneous or recent (i.e. last 3 months) participation in another clinical trial or blood donation, to allow full recovery of blood volume [66]

• Any reported recent (i.e. last 6 months) shift (>1 kg) in body mass

• Any reported tendency towards keloid scarring

• Any reported bleeding disorder

• Females known to be pregnant or planning to become so over the course of the study

• Females with oral or implanted contraceptives fitted within 6 months of participation [67]

• Females who are breastfeeding

### Statistical Approach/Power Estimation

The number of research participants to be recruited was estimated based upon a worthwhile effect dictated by the smallest shift in energy balance necessary to induce chronic weight loss. Specifically, one of the most similar studies to the proposed work applied doubly-labelled water to measure average daily energy expenditure in a population not dissimilar to that planned [38], from which a mean of ~12000 kJ·d^-1 ^might be expected with a standard deviation in the region of ~2000 kJ·d^-1^. The daily breakfast to be consumed in this trial will provide in excess of ~3000 kJ·d^-1 ^and our pilot work using this breakfast indicates that this is likely to stimulate metabolism in the lead up to lunch by ~150 kJ·d^-1 ^and reduce energy intake at lunch by ~150 kJ·d^-1^, relative to continued fasting. Therefore, for breakfast consumption to exert a worthwhile effect on net energy balance (i.e. sufficient to compensate for the energy it provides directly), physical activity energy expenditure would need to increase and/or subsequent energy intake to decrease by a further 2700 kJ·d^-1^. Using the above figures, a worthwhile increase in energy expenditure would require ~14 participants in each treatment group to confer a 90% probability of detecting such an effect statistically using a two-tailed *t*-test with an alpha level of 0.05. A total of 70 participants will therefore be recruited for the main study treatment arms in view of the 14% drop-out rate reported by Schlundt *et al*. (1992) when placing similar demands on volunteers [51], thus aiming to achieve at least 60 participants to provide sufficient statistical power even when the overall breakfast *versus *no breakfast groups are stratified according to FMI (with baseline breakfast habits, gender and age included as co-variates in the analysis). Nonetheless, to minimise the negative impact of loss to follow-up on validity, participants will be advised at trial enrolment to very carefully consider the required investment of time and effort relative to their current and forthcoming commitments outside of the trial, such that exclusions based on likely withdrawal can be made prior to randomisation [68]. Any unforeseen circumstances or withdrawal of consent subsequently resulting in loss to follow-up will be documented fully in the final trial report. Data collected from these individuals to the point of loss will then be compared with those who complete each treatment to determine whether the overall conclusions of the trial may be generalised beyond populations reflective of the latter (i.e. to anyone willing to be randomised).

As with the primary outcome measure, secondary variables will also be analysed using either paired or independent *t*-tests applied to simple summary statistics between groups or trials, respectively (e.g. fasted/peak values, incremental area under curve, average value over 24 h, *etc*.). Given that these sample size estimations are based on a primary outcome that inherently displays a relatively large inter-individual variability, it is anticipated that the more consistent responses of secondary variables will also be detectable with the selected sample size.

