
The bowl of pasta will be refilled every 10 minutes to minimise any visual feedback in the regulation of appetite. To gain additional insight regarding psychological reward and food hedonics, a validated labelled magnitude scale [76] will be administered following the first and last mouthful of this meal to reliably assess the degree of 'pleasantness' associated with ingestive behaviour. The 3 hour post-prandial period will then be repeated exactly as following breakfast (but without the 15-30 minute samples) to track metabolic responses to lunch.

***Objective ii - ***Phase II of testing will commence within 3-28 days after completion of each participants' second trial under Phase I of testing (thus using participants' breakfast trial along with the measures described above as a baseline). This trial schedule will again be used for all participants other than for eumenorrheic women, who will follow the same restrictions as described above and therefore occasionally be required to complete their first trial under Phase II prior to the completing the second trial under Phase I. In such cases, these participants' 6-week intervention will simply be deferred for two weeks (i.e. enabling completion of Phase I) to allow follow-up measures to be taken at the same stage in the menstrual cycle. The first visit under Phase II will begin with participants again arriving in the laboratory at 8 am (±1 h) having adhered to the same standardisation procedures as described for Phase I. Measurements of body mass and adiposity based on hip and waist circumference (i.e. widest gluteal girth & mid-point between lowest rib and iliac crest, respectively), sagittal abdominal height (using a Holtain-Kahn calliper at the iliac crest) and body composition via DEXA (Hologic Discovery W) will also be made at this visit, before a small (~1 g) sample of subcutaneous adipose tissue will be acquired using a 14 G needle to determine basal expression of key genes related to appetite and physical activity regulation (e.g. adiponectin and leptin) and energy expenditure (e.g. UCPs).

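### Lean-mass variation within FMI strata is adjusted for only through gender, although baseline DEXA fat-free mass is measured: an optional gain in precision, not an error

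*Protocol article*

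**What the plan says.** All references are to the protocol article.

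- **Sizing** (Statistical Approach/Power Estimation). The calculation uses average daily energy expenditure of about 12000 kJ/d, which "might be expected with a standard deviation in the region of ~2000" kJ/d. The worthwhile effect is that "physical activity energy expenditure would need to increase and/or subsequent energy intake to decrease by a further 2700" kJ/d. About 14 per group are said "to confer a 90% probability of detecting such an effect statistically", with a "two-tailed *t*-test with an alpha level of 0.05". Seventy are recruited so that at least 60 complete.
- **Analysis terms** (same section). The 60 are meant to suffice when the two arms are stratified by FMI, "with baseline breakfast habits, gender and age included as co-variates in the analysis". The next paragraph describes t-tests on summary statistics for the primary and secondary variables and mentions no covariates. It calls the sizing outcome "a primary outcome that inherently displays a relatively large inter-individual variability".
- **Weight status** (Participants/Eligibility). Half the cohort is normal weight and half obese. Gender-specific DEXA FMI cut-offs define the strata, chosen so as to control for lean tissue, and separate analyses are planned. Four block schedules balance weight status and breakfast habit between arms.
- **Measurements** (Experimental Protocol). RMR is measured in Phase I. At the first Phase II visit, "body composition via DEXA (Hologic Discovery W) will also be made at this visit". Free-living expenditure is recorded in the first and last week of the intervention, so never before it starts.

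**The concern.** The outcome behind the sample size varies widely between people, and the trial has no pre-intervention free-living value to adjust for. The next-best predictors are baseline measures of body size and resting metabolism. Both are collected, yet neither is among the three named covariates. FMI does not fill the gap, because it indexes fat and is chosen to be separate from lean tissue.

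What is at stake is interval width. Objective ii turns on how far breakfast is offset by changes in expenditure and intake, and partial compensation well below 2700 kJ/d would be informative. At 30 per arm, the unadjusted 95% interval has a half-width of about 1034 kJ/d, roughly a third of the 3000 kJ breakfast. At 15 per arm it is about 1496 kJ/d, roughly half. A baseline covariate already in hand could narrow this at little cost, and it is better named before the data are seen than added afterwards.

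**Working it through.** **Inputs from the documents.** Difference 2700 kJ/d, SD 2000 kJ/d, two-sided alpha 0.05, power 90%, dropout 14%, at least 60 completers. Assuming 1:1 allocation and equal halves, that is 30 per arm overall and 15 per arm in each FMI stratum.

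**Step 1: reproduce the plan's figure.**
- Normal approximation: n = 2 × (1.960 + 1.282)² × 2000² / 2700² = 11.5, so 12 per group.
- Noncentral t: 12.6, so 13 per group. The stated figure of about 14 gives power of 93.0%.
- Dropout: 60 / 0.86 = 69.8, so 70, as stated.

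The calculation uses the unadjusted SD and takes no credit for any covariate.

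**Step 2: power as planned, with no added covariate.** For 2700 kJ/d, t-test power is 94.6% at 15 per arm and 99.9% at 30 per arm. The difference detectable with 90% power is 2453 kJ/d at 15 per arm and 1702 kJ/d at 30 per arm. Both lie below the 2700 target.

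**Step 3: does the lean/obese mix matter?** Suppose 2000 were only the within-stratum SD and the stratum means differed by D. The unstratified SD would be √(2000² + D²/4). For assumed D of 1000, 2000, 3000 or 4000 kJ/d this is 2062, 2236, 2500 or 2828, and power at 30 per arm is still 99.9%, 99.6%, 98.4% or 95.3%. The FMI stratification removes this between-stratum part, which is 6%, 20%, 36% or 50% of the variance.

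**Step 4: effect of adding fat-free mass.** Let R² be the share of the variance left after FMI stratum, habit, gender and age that fat-free mass explains. The documents give no value, so 10%, 25% and 40% are assumed. Interval width and detectable difference are multiplied by √(1 − R²), which does not depend on the starting SD. The equivalent gain in participants is 1/(1 − R²).

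| Assumed R² | √(1 − R²) | Reduction | Equivalent participants |
|---|---|---|---|
| 10% | 0.949 | 5% | 1.11 × |
| 25% | 0.866 | 13% | 1.33 × |
| 40% | 0.775 | 23% | 1.67 × |

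**Step 5: illustration in kJ/d.** Starting from SD 2000:

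| Assumed R² | Detectable, 30 per arm | Detectable, 15 per arm | 95% half-width, 30 per arm |
|---|---|---|---|
| 0 | 1702 | 2453 | 1034 |
| 10% | 1615 | 2327 | 981 |
| 25% | 1474 | 2124 | 895 |
| 40% | 1319 | 1900 | 801 |

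The half-width is 2.00 × 2000 × √(2/30), multiplied by √(1 − R²). At 15 per arm with no covariate it is 2.048 × 2000 × √(2/15) = 1496.

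The kJ/d values are illustrative. R² is defined after gender and age, whereas 2000 is an unadjusted SD, and the residual SD after the named terms is not given. The percentages in Step 4 are the safer reading. Both tables ignore the one degree of freedom spent.

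**The case against.** **Nothing here is wrong or contradictory in itself.** A randomised comparison that leaves out a prognostic covariate is still unbiased, and the stated power is met without it. The list stands in a parenthesis of a condensed article that does not call it complete, and a fuller analysis plan could add terms. This stands, and it is why the point is only an optional improvement.

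**The lean/obese contrast is already handled.** A reader might infer that recruiting both normal-weight and obese people leaves that contrast in the error term. The documents do not support this: weight status is balanced by the block schedules, and FMI strata are used in the analysis. What remains is lean-mass variation within strata.

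**The outcome may be activity expenditure alone.** The central aim in the Background is physical activity energy expenditure, and the worthwhile shift is stated in those terms. A reader might take the Background's "difference between resting energy expenditure measured using the whole-body calorimeter and average daily free-living energy expenditure" to show that resting expenditure is part of this trial's outcome. That phrase describes how a cited study derived activity; it does not define the outcome here. If resting expenditure is removed before analysis, the gain may be smaller.

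**Baseline DEXA is not wholly untouched by allocation.** Pre-visit diet follows the assigned arm in Phase I, and the DEXA visit uses the same standardisation. This stands for RMR as well as for fat-free mass, and no passage shows that fat-free mass is the less affected of the two.

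**Plain t-tests carry no covariates.** This also stands. Read literally, the t-test paragraph would leave any added covariate unused, so the two paragraphs must be reconciled first.

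**Conclusion.** The point holds in a narrow form. The named covariates and the FMI strata leave within-stratum lean-mass variation adjusted for only through gender, although a baseline measure is in hand and the outcome has no pre-intervention value.

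The consequence is wider intervals than necessary: about 5%, 13% or 23% wider-than-needed precision is recoverable, as a reduction in width, if R² is 10%, 25% or 40%. Those R² values are assumptions, and the gain may be less for activity expenditure alone. No case is made for energy intake, for which nothing was calculated.

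A reader might infer that the trial is underpowered or its sample size wrong. On the plan's own SD neither follows: the figure of about 14 per group reproduces to within one or two participants, and power for 2700 kJ/d exceeds 90% even within one FMI stratum. Severity: optional, nearly free improvement.

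**What to change.** In Statistical Approach/Power Estimation, replace the mismatch between named covariates and plain t-tests with one stated model for free-living energy expenditure. Its terms would be treatment, FMI stratum, baseline breakfast habit, gender, age and baseline DEXA fat-free mass. Add a sensitivity analysis adjusted for RMR.

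State beside the model that the DEXA visit follows a pre-visit diet standardised by assigned arm, so the covariate is a pre-intervention measure but not strictly a pre-allocation one. State also whether the outcome modelled is total or activity expenditure, since the expected gain depends on it.

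The cost is a few lines of text and one degree of freedom. No new measurement and no change to the sample size is needed.
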